#### Co-design workshops

Audio recordings of workshops will be transcribed verbatim. Transcripts will be reviewed alongside facilitator notes to capture all key information and decisions. This will enable an audit trail and reporting of when, how, and why key development decisions were made. Following the conduct of each co-design workshop, a summary document will be prepared to enable Hark 2 to iteratively develop an intervention prototype ahead of usability testing.

### Stage 2 sampling and eligibility criteria

#### Stage 2 sampling strategy

Up to 40 patient participants listed for major surgery (from a range of surgical specialties) will be recruited to take part in the study from the two participating Trusts. This target sample size is informed by published guidance for pilot and feasibility studies [38] and accounts for potential drop-out (~ 20%).

HCP participants will be recruited from each site and required to undergo training (training co-designed during stage 1) and either promote use of the digital intervention by patients or provide support to those using it. The number of stage 2 HCP participants will be guided by stage 1 findings (i.e., following consensus on who should fulfil what role).

#### Stage 2 eligibility criteria

*Patient participants*. Patients aged ≥18 years preparing for major surgery (as indicated by NICE CG45 [36]) and available for a minimum of 4 weeks prior to planned surgery; ASA (American Society of Anaesthesiology) fitness for surgery ≥ grade 2; At least one health risk behaviour amenable to prehabilitation (e.g., current smoker); able to access and utilise the internet at home; able to communicate in spoken and written English, and able to provide informed written consent will be eligible to take part in the study. Participants who are pregnant or planning pregnancy; have severe mental illness (under active investigation or treatment by mental health services and/or preventing written informed consent); already undergoing prehabilitation or have a preference for an alternative mode of support (e.g., an in-person, face-to-face service); and those receiving end-of-life-care will be excluded. Where a patient participant has a safety contraindication to unsupervised exercise training based on ACSM criteria for clinical exercise testing and prescription [39], they will be excluded from the structured exercise component of the intervention but will be given access to other components of the intervention.

#### Healthcare professional participants

Perioperative team members currently caring for patients approaching major non-cardiac surgical intervention will be eligible to take part. A willingness to take part in training to support promotion and/or delivery of the intervention is essential.

### Stage 2 recruitment and consent

#### Patient participants

Patients listed for major surgery will be screened for eligibility by perioperative teams utilising electronic hospital records. Potential participants will be approached by telephone to explore interest. Those interested will be given a patient PIS sent by post or email. Interested patients will receive a follow-up telephone call by a team member within 7 days allowing time to receive, read and understand the study information and consider participation. Those who would like to participate will be invited to undertake a screening and baseline assessment (visit 1) where they will be given an opportunity to ask questions and complete a consent form with a study team member. Patients who decline participation at that stage will undergo routine preoperative care and their reason for non-participation will be recorded if they elect to provide one.

#### Healthcare professional participants

Perioperative team members at each site will be contacted by email inviting them to take part in the study with a follow-up after 7 days providing time to consider participation. The email will provide a HCP PIS and those who are interested in taking part will complete a consent form with a study team member and be invited to begin the intervention HCP training package.

### Stage 2 outcome measures

#### Primary outcomes

*1*. *Feasibility*. Feasibility will be determined by assessing participant recruitment and retention rates, time taken to recruit to the target sample size, and rates of intervention uptake and completion, including number of patients completing all relevant components of the intervention.

Feasibility of the training intervention will be determined by assessing HCP participant recruitment and retention rates, time taken to recruit to the target sample size, and rates of training intervention uptake and completion, including willingness to refer to the intervention and continue to promote and support patient participants with the intervention.

*2*. *Fidelity*. Fidelity of delivery will be assessed by collecting data relating to intervention usage by patient participants, including when components were accessed, revisited, and for what length of time. Fidelity of receipt and enactment will be assessed qualitatively via semi-structured interviews with patient participants.

Fidelity of delivery of the training intervention will be assessed by audio recording delivery of the training to ensure all intervention components are delivered per protocol using an intervention fidelity checklist [40]. Fidelity of receipt and enactment will be assessed qualitatively via semi-structured interviews with HCP participants.

*3*. *Acceptability*. Acceptability will be assessed quantitatively and qualitatively. In terms of patient participants, data will be collected on the number of logins over the intervention period and the number of interactions with facilitating HCP participants. In terms of HCP participants, data will be collected on the number of HCPs who consent to take part in the study/be trained and who complete training. Semi-structured interviews using the TDF as an analysis framework will obtain participant (patients and HCPs) views and experiences of the intervention, including their experiences of using/interacting with the intervention, perceived barriers, and facilitators to using it and suggestions for ways in which it could be improved.

#### Secondary outcomes

Data will be collected on the following secondary outcomes: Patient activation (Patient Activation Measure [PAM]); physical activity (International Physical Activity Questionnaire [IPAQ], accelerometery data from integrated wearable device); smoking status (self-reported); alcohol consumption (units per week); nutritional (PG-SGA) and dietary status (Dana-Faber healthy eating questionnaire, modified for personal consumption); sleep (Pittsburgh Sleep Quality Index); exercise capacity (6-minute walk test [6MWT], 30-second sit to stand repetitions, grip strength, maximum inspiratory pressure); Psychological wellbeing (Hospital Anxiety and Depression Scale [HADS]); Health-related quality of life (HRQOL using SF-36v2 and EQ-5D-5L); postoperative mortality and morbidity (30 and 90 day mortality, Comprehensive Complication Index [CCI]); and length of stay and readmission (length of hospital stay, length of critical care stay, days at home [or usual residence] within 30 days of surgery [DAH_30_]). The feasibility and sensitivity of data collection for these outcome measures will be explored to identify candidate primary outcome measures for a future randomised controlled trial of the intervention.

In addition, semi-structured interviews will qualitatively assess feasibility and usability of the integrated wearable device in support of programme components and perioperative biometric monitoring.

### The digital intervention (iPREPWELL)

The content and format of the digital intervention components will be informed by the systematic development process undertaken during stage 1 of the study. However, the intervention will have the following features and functions:

Intervention duration–the time between participants being listed and having their surgery is between 4 and 8 weeks on average, therefore the duration of the intervention will run in accordance with this timeline. Access will be continuous during this time and up to 3 months postoperatively.Intervention components offered to participants will be personalised during registration, i.e.., non-smokers will not be offered content related to smoking.Given the tendency for clustering of health risk behaviours and limited preoperative timeframes in surgical populations, intervention components will be designed to run simultaneously. They will be delivered using textual, audio, and visual material. Decisions about the specific mode of delivery and format of each intervention component will be informed by findings from the systematic development process.

Additional intervention features could include:

Incorporation of a wearable physical activity monitoring device to facilitate self-monitoring and real-time participant feedback. The most appropriate device will be agreed in collaboration with participants during phase 1 of the study.An online forum facilitating interaction with facilitators and other participants.Direct messaging between the facilitating HCP and participants to prompt behavioural change and provide support.Access to educational content in the context of the perioperative journey (e.g., ‘digital surgery school’).

The physical activity and exercise component of the intervention will be included for all participants reflecting the high rates of physical inactivity within this clinical population, and the potential to enhance aspects of physical fitness in surgical populations [11]. Only participants with identified contraindications to physical activity or exercise will be excluded from this component of the intervention. This intervention component will support increased physical activity and remotely supervised structured exercise before surgery including aerobic, resistance/strength and inspiratory muscle training. Specifically, this will include:

Provision and use of home-based exercise equipment, including resistance bands and an inspiratory muscle training deviceUtilisation of the integrated wearable device to guide training sessions and provide feedback e.g., heart-rate guidance for aerobic training sessions

Patients will be encouraged to login throughout the intervention period to engage with the various components to promote/maintain motivation and volition to support health behaviour change. It is anticipated that patients will require a level of remote HCP support throughout the timeline of the intervention. What this involves will be determined during stage 1 of the study, the developmental process. HCP participants will take part in training prior to supporting patient participants.

### The training intervention

The content and format of the training intervention for HCPs will be informed by the systematic development process undertaken during stage 1 of the study. Not wishing to pre-empt the outcome of stage 1 of the study, training is likely to incorporate health behaviour-specific content to target knowledge, and skills-based training to facilitate promotion of the intervention during routine care and to facilitate the provision of support to patients throughout the intervention period. The training intervention, as with the patient intervention, will be theory and evidence-informed with reference to the BCW [31].

### Stage 2 study visits

Fig 3 provides an overview of stage 2 of the study (feasibility study).

**Fig 3 pone.0277143.g003:**
[figure not shown]
Overview of stage 2 of the study (feasibility study).

#### Visit 1 (screening and baseline assessment)

Patient participants will attend the hospital site to undergo a baseline assessment process (incorporating a safety screen for remotely supervised exercise based on ACSM guidance [38]) and registration onto the intervention. The assessment will combine clinical, health behaviour and exercise capacity elements as presented earlier. It will be conducted by a facilitating HCP participant and at least one research team member. The methods for physical activity and exercise capacity assessments are provided in our (S3 File). Following visit 1, patient participants will utilise the digital intervention at home with remote support by a trained HCP participant.

#### Visit 2 (preoperative assessment)

Visit 2 will be scheduled prior to surgery to assess changes in health behaviours (e.g., physical activity) following platform usage. The visit will be conducted at the hospital site by at least two research team members. Data collected will mirror visit 1 ([S4 File]).

#### Visit 3 (postoperative assessment)

Visit 3 will be scheduled at 30 days postoperatively to assess change/maintenance of health behaviours and to collect postoperative outcome data. The visit will be conducted at the hospital site by at least two research team members. Data collected will mirror visits 1 and 2.

### Stage 2 quantitative data collection

Data will be collected, where possible, as an electronic case-record form (e-CRF) within the online intervention. Completion of these will be scheduled as part of intervention utilisation e.g., the registration process will include e-CRF 1. Data will be entered by patient participants, with additional data input by HCP participants and study team members, where appropriate.

Additional data will be collected on intervention utilisation, e.g., number of logins, duration of session, completion of individual intervention components, and information entered by participants during intervention usage. The integrated physical activity wearable device will collect data that will be uploaded into the intervention platform, stored, and made available to participants, e.g., daily recorded step counts.

### Stage 2 qualitative data collection

Up to 40 patient participants and all participating HCPs will be invited to take part in a semi-structured interview with a research team member. This component of the study is optional (i.e., patient participants can take part in the intervention study and refuse participation in the qualitative study). In keeping with stage 1, companions will also be included if patient participants wish and will complete a stage 2 consent form to allow their interview contributions to be included in the analysis. All interviews will be audio recorded and transcribed verbatim.

To facilitate an early health economic analysis, HCP participants will be asked to complete a diary of activity in terms of support provided to patient participants.

### Stage 2 data analysis

#### Quantitative data

Data will be summarised descriptively using mean and SD or median and IQR for continuous variables, and count and percentage for categorical variables. As this is a feasibility study, the level of missing data will be documented but no imputation undertaken.

An initial health economic analysis will be conducted to focus on costs of intervention delivery to inform design of a future efficacy study.

An initial exploratory analysis of pseudo anonymised perioperative wearable data will be undertaken utilising machine learning techniques supported by Telstra Health UK.

#### Qualitative data

Qualitative data will be thematically analysed using the TDF. Two members of the research team will independently code and analyse interview transcripts. The same procedure will be undertaken as described during stage 1 to develop a coding strategy.

A detailed description of how data will be handled is provided in (S4 File).

### Study management

A study management group (SMG) will be established by the chief investigators prior to the commencement of stage 2 of the study with representation from the sponsor, participating sites and institutions, patient representatives recruited during stage 1, and research partners. The group will oversee the conduct of the feasibility study and meet monthly, or as required.

### Study safety considerations

#### Stage 1

Participation during Stage 1 is anticipated to present a low risk of adverse events (AEs) for participants. Potential AEs occurring during stage 1 activities will be assessed, graded, and followed up until resolution by the study team in keeping with study sponsor and UK Good Clinical Practice (GCP) guidance.

#### Stage 2

Potential AEs occurring throughout the duration of stage 2 of the study, whilst the intervention will be assessed, graded, and followed up by the research team until resolution in keeping with sponsor and GCP guidance.

Risk to patient participants is most likely to originate from participation in the structured exercise training programme. Other intervention components are not anticipated to lead to AEs. The overall risk of AEs relating to exercise is considered low. This is based on a growing body of evidence demonstrating the safety of structured exercise training (including aerobic, resistance and inspiratory muscle training) in surgical populations [41]. This is in addition to the safety profile of several hundred maximal effort cardiopulmonary exercise tests conducted in the study target population at participating sites and nationally [42].

Despite this, we are mindful of the additional risk this poses in comparison to directly supervised exercise interventions. The following measures are planned to mitigate this as far as possible:

An independent clinician will review all serious adverse events (SAEs) and report to the study management group.Participants will be formally risk assessed to confirm safety for participation based on international criteria for exercise training and testing [42] and the expertise of an active face-to-face surgical prehabilitation service.Participants will undergo several functional capacity assessments face-to-face with trained healthcare professionals prior to commencing remotely supervised training.The exercise intervention will begin with clear, co-designed safety instructions relating to both undertaking physical activity safely and undertaking activity outside the home environment.Clear channels for participants will be provided to raise non-emergency concerns with HCP facilitators and the research team and how to access help in an emergency.The exercise component of the intervention will be scaled to participant capabilities and progression in intensity will be participant, rather than facilitator lead.Wearable data collected during training sessions will allow intensity monitoring and adjustment as required.

### Stage 2 participant discontinuation and withdrawal

Stage 2 participants will be free to withdraw from the study at any stage without providing a reason.

Participant discontinuation will occur with any of the following:

Completion of the stage 2 study protocol.Acute Illness requiring hospital admissionDeath of participant or commencement of end-of-life careDecision to cancel surgical interventionLoss of capacity to consent to continue participationParticipant decision to withdrawInvestigator decisionStudy management group or chief investigator decisionSevere non-compliance to protocol as judged by the investigator and/or sponsorSafety reasons

If a participant wishes to withdraw or is discontinued from the study, the following procedures will be observed:

Participants will be offered the chance to take part in a semi-structured interview to provide their reasons for withdrawal from the process to allow learning. Participants will be free to decline this interview without providing a reason.Withdrawal of consent/ discontinuation of the study will be clearly documented in study documentation and the participant’s medical record.No further clinical data will be collected from the participant. However, existing clinical data held will be retained and used for the research.Patients will continue with standard of care treatment as recommended by their treating team.

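### Discontinuation for acute illness with admission, and for other listed reasons, ends clinical data collection: later outcomes are lost in patients doing badly, and the rule conflicts with adverse-event follow-up

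*Protocol article*

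**What the plan says.** The section on stage 2 discontinuation and withdrawal opens its list of triggers with "Participant discontinuation will occur with any of the following". The list includes acute illness leading to admission, safety reasons, severe non-compliance, investigator decision and cancelled surgery. Its first item is completion of the stage 2 protocol, so it runs through follow-up and is not confined to the period before surgery.

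The consequences are introduced by "If a participant wishes to withdraw or is discontinued from the study, the following procedures will be observed", so they apply to discontinued participants as well as to those who withdraw. One consequence is "No further clinical data will be collected from the participant", followed by "However, existing clinical data held will be retained and used for the research". No exception is stated for outcomes available from hospital records or for safety follow-up.

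The secondary outcomes include "postoperative mortality and morbidity (30 and 90 day mortality, Comprehensive Complication Index [CCI]); and length of stay and readmission". The length-of-stay and readmission group includes days at home within 30 days of surgery (DAH30). Visit 3 is at 30 days after surgery. The secondary outcomes are to be explored as candidate primary outcomes for a later randomised trial, and the study objectives add estimates of variability to size that trial. The quantitative analysis section says missing data will be documented and not imputed.

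Under the stage 2 safety considerations, adverse events are to be "assessed, graded, and followed up by the research team until resolution", and an independent clinician is to review every serious adverse event.

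**The concern.** Discontinuation and the end of data collection are treated as one act, and several of the triggers are related to how the patient is doing. An acute illness serious enough for admission is linked to readmission, days at home, complications and death, all of which the study sets out to record. Stopping collection at that point makes the missing data informative: what remains complete comes disproportionately from patients whose course was smooth. Severe non-compliance has a similar effect on later behavioural measurements.

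Two things are at stake. The first is the value of the secondary outcome data for planning the next trial. If patients with a poor course are under-represented, mean DAH30 will tend to look too good and its spread too small. The second is consistency of the safety instructions. For a participant admitted with an acute illness that is also an adverse event, one section ends clinical data collection and another requires follow-up to continue.

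**Working it through.** The protocol states no figure for this point that could be reproduced. The sample size section gives up to 40 patients, allowing for about 20% drop-out, which implies 40 × (1 − 0.20) = 32 with complete data. The base number is not stated, and neither is whether the allowance covers discontinuations.

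**Following the rule for individual patients**

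- *Acute readmission after discharge.* The trigger is met, so discontinuation is mandatory and collection stops. The readmission itself and all earlier data are kept. Lost: the rest of the 30-day window, later complications, visit 3 if not yet held, and later mortality.
- *Acute admission before surgery.* The trigger is met before any operation. If surgery then goes ahead, every postoperative outcome is lost.
- *Complication during the surgical stay.* The patient is already in hospital for a planned admission. The trigger is not clearly met, so these data are not clearly affected.
- *Cancelled surgery.* Postoperative outcomes are undefined. Only visit 2 and other preoperative data can be lost.

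**DAH30 for one patient (assumed course).** Index stay 8 days, readmission from day 14 lasting 7 days.

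- True value: 30 − 8 − 7 = 15.
- Known when collection stops at day 14: 14 − 8 = 6 days at home, with 30 − 14 = 16 days unobserved.
- The value can therefore only be placed between 6 and 6 + 16 = 22, so it is missing. The figure of 22 would arise only if the readmission were ignored, which is unlikely because discontinuation must be documented.

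**Number affected.** The document gives no rate of acute admission. Assume r = 5% to 15%.

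- Expected number: 40 × 0.05 = 2 to 40 × 0.15 = 6.
- Chance that at least one patient is affected, 1 − (1 − r)^n, at r = 5%: 1 − 0.95^40 = 0.87 with n = 40, or 1 − 0.95^32 = 0.81 with n = 32.

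**Possible effect on DAH30 (illustration only).** Assume a mean of 22 days without readmission and 12 with it, an SD of 4 within each group, and that every affected patient's value is missing. Patients with complete data then show mean 22 and SD 4. For all patients, the mean is 22 − 10r and the SD is √(16 + r(1 − r) × 100).

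| r | Mean, all patients | Overstatement (days) | SD, all patients |
|---|---|---|---|
| 5% | 21.5 | 0.5 | 4.56 |
| 10% | 21.0 | 1.0 | 5.00 |
| 15% | 20.5 | 1.5 | 5.36 |

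Sample size for a comparison of means is proportional to the variance. A later trial sized on SD 4 would have 16/20.75 = 77%, 16/25 = 64% or 16/28.75 = 56% of the number it needed. The direction follows from the assumption that readmitted patients have fewer days at home; the size depends wholly on the assumed values.

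**Safety text side by side.** The safety section sets resolution as the end of adverse-event follow-up by the research team. The discontinuation section sets discontinuation as the end of clinical data collection. Where an event causes discontinuation, the second normally comes before the first, and neither section refers to the other.

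**The case against.** The strongest reply is that the wording does less damage than it first suggests. Much of that stands.

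- A reader might infer that any hospital admission triggers the rule, so that patients with postoperative events are dropped. The trigger is acute illness requiring admission. The planned surgical admission does not meet it, and stay, critical care and complications within that admission are not clearly affected.
- A reader might infer that the triggering event goes unrecorded. Discontinuation must be documented and existing data are kept, so the readmission or death would normally be known. The loss is of what comes afterwards.
- A reader might apply the introduction's major morbidity of 15% to 40% and count 6 to 16 of 40 patients lost. That is background morbidity; nothing discontinues a patient for a complication as such.
- A reader might infer that the primary feasibility results are corrupted. Retention and completion are counts, and a discontinued patient can be counted as not retained or not completed. No passage removes such patients from a denominator, and platform-usage logs are not clearly clinical data.
- The bar concerns data collected from the participant, which may be meant to leave record look-up and safety reporting open. Safety follow-up is tied to sponsor and Good Clinical Practice guidance, and data handling is detailed in a supplementary file not shown. So the text does not show that serious adverse event follow-up would actually stop.
- The affected outcomes are secondary, in a descriptive single-arm study that does not assess efficacy and allows for about 20% drop-out.

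What does not stand is the suggestion that nothing needs changing. The text does not say that record look-up continues, and the contrast with data already held suggests that collection simply ends. A drop-out allowance protects the number of patients, not their representativeness. An analysis plan cannot recover data that were not collected.

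**Conclusion.** The point holds as a conflict between stated rules and as an avoidable, outcome-related loss of later follow-up. It is a cheap improvement to make before stage 2 enrolment, not a flaw that undermines the feasibility aims.

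About 2 to 6 of 40 patients would be affected if 5% to 15% have an acute admission; the rate is an assumption. The effect on mean DAH30 and its SD is illustrative only. The conclusion also assumes that the data-collection bar is applied as written. If the full protocol or the data-handling supplement already permits record-based collection and safety follow-up after discontinuation, only the article's wording needs correcting.

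The documents do not support the stronger conclusions that postoperative outcomes are generally missing in patients who have complications, that the primary outcomes are invalid, or that serious adverse events would go unfollowed.

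**What to change.** Reconcile the secondary outcomes, stage 2 safety and discontinuation sections by defining two separate events: stopping the intervention and ending data collection. Unless the participant withdraws consent to data collection, continue after discontinuation:

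- outcomes available from records (mortality, complications, length of stay, readmission, DAH30) where surgery took place;
- adverse-event follow-up to resolution, with the independent review of serious events unchanged;
- visit 2 and visit 3 assessments where the participant is willing.

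Report discontinuations by reason. Whether any of the listed events should stop the intervention is a clinical matter for the investigators and is not addressed here.

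The cost is one ethics amendment with matching information-sheet wording, and record look-up and data entry for a few patients. Since 90-day mortality falls after the last study visit at day 30, some means of obtaining it outside the visits is needed in any case.
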